#### Secondary outcome measures

1) EuroQol classification system and VAS rating personal health. A cost-utility analysis will be performed using QALY's based on the EuroQol questionnaire, which has been validated in many studies and is easy to fill out [41,42,51]. The EuroQol will be measured twice a week during the first four weeks and at all follow-up moments. Patients describe their general health status using the EuroQol classification system, consisting of 5 questions on mobility, self care, usual activities, pain/discomfort, and anxiety/depression [44]. From the EQ-5D classification system, the EQ-5D utility index will be calculated [43]. This utility measure reflects how the general public values the health status described by the patient, which is preferred for economic evaluations from a societal perspective. Patients also rated their personal health using a visual analog scale (VAS) ranging from worst imaginable health to best imaginable health.

2) Short-Form 36 (SF-36). Quality of life was also assessed using the RAND-36 questionnaire. This is a generic health status questionnaire, which can easily be filled out at home. The questionnaire consists of 36 items on physical and social functioning has 8 domains; 1) physical functioning, 2) physical restrictions, 3) emotional restrictions, 4) social functioning, 5) somatic pain, 6) general mental health, 7) vitality, 8) general health perception. This questionnaire has been used frequently and was validated in studies on low back pathology and surgery [33-37]. From the RAND-36, the SF-6D utility index was calculated. Like the EQ-5D, this SF-6D reflects the general public's valuation of the health described by the patient. The SF-6D is a recent instrument that has not been used much yet, but it richer classification system could make it a more sensitive utility measure than the EuroQol measure.

3) Sciatica Frequency and Bothersome Index (SFBI). This is a scale from 0 to 6, which can assess the frequency (0 = not at all to 6 = always) and bothersomeness (0 = not bothersome to 6 = extreme bothersome) of back and leg symptoms. The sum of the results of four symptom questions yields both indexes, ranging from 0 to 24: leg pain; numbness and/or tingling in the leg; weakness in the leg or foot; pain in the back or leg while sitting. [17].

5) PROLO-scale. This scale measures the evaluation of the research nurse of the functional-economic status of the patients. This parameter has been used in studies on the difference in functional outcome between different techniques of lumbar spine fusion [40].

6) VAS pain in the back. This parameter measures the intensity of the pain in the back experienced during the week before visiting the research nurse. Assessment will be based on a horizontal 100 mm scale varying from 0 mm, 'no pain in the back', to 100 mm, 'the worst pain ever'. Patients do not see the results of earlier assessments and will score their pain during the visit. This parameter is included because a lot of patients with LSRS also have back pain in varying intensities, which can change after surgery or conservative treatment.

#### Other outcome measures

1) Costs. The societal costs during the first year will be estimated in accordance with the recent pharmacoeconomic guideline [47,48]. The costs of hospital admission and surgery will be based on an integral top-down cost analysis in three large regional participating hospitals (aggregated according to the total number of patients per department). From this institutional analysis, the constant costs per admission and the variable costs per admission day will be estimated. From these constant and variable costs, the individual costs of hospital admission and surgery for all patients can be estimated, using the duration of the hospitalization. In the study an MRI is performed in all cases. The costs of this MRI will only be calculated for patients undergoing surgery, because in the normal situation MRI would only be performed when a surgical indication exists.

Patients will register other health care needs in a diary (including physiotherapy, visits to GP's and specialists, nursing care and medication). Each diary covers a period of 3 months and will be discussed with the patient during the follow-up visits to the research nurse. The volume of health care will be assessed using standard prices [48].

In the diary the patient will also register direct non-medical costs (including time costs, travel expenses and domestic help). To estimate productivity costs the patients will also report absenteeism in the diary. At the follow-up visits, the research nurse will register the work situation, work efficiency and gross wages. Absenteeism will be valued according to the friction-cost method.

2) Incidence of (re-) surgery. One of the goals of the policy for group B is to avoid surgery while achieving at least the same effects. The surgical rate is therefore an indication of the success or failure of this policy. The incidence of re-operation at the same disc level in group A will be an indication of the failure rate for surgery.

3) Side-effects or complications that are ascribed to the treatment are recorded by the patients, their treating physicians and the research nurses.

4) MRI findings. The results of the differences between the baseline MRI and the MRI made 52 weeks after randomization are important secondary outcome measures. The difference in size of the disc herniation (in mm), nerve root compression, and amount of scar tissue will be registered. Failures of surgery can be recognized by inadequate disc removal or decompression of the nerve. The data will be gathered, using a standardized CRF, which will be filled out by the local radiologist, orthopaedic- or neurosurgeon and (neuro-) radiologist

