In summary, consensus is missing on the preferred timing of disc surgery, due to insufficient evidence that a prolonged conservative care strategy is effective. More insight is needed into the potential short-term effects of a relative early surgery strategy, as compared to an extended wait-and-see period. In particular the effects on the return to work or resumption of previous daily activities as well as the complications of both strategies have not yet been investigated.

The main goal of this comparative study is to investigate whether the completion of a 6–12 weeks period of lasting radicular pain constitutes a solid indication for surgery and is superior to prolonged conservative care. A secondary goal is to identify possible subgroups of patients who will substantially benefit from one of the proposed treatment strategies. The cost-effectiveness results will be a trade-off between a quicker relief of leg pain in the surgery group versus the advantage of lower costs and avoiding the negative effects of surgery in the conservatively treated group. The difference in disease related quality of life depends on the duration of persisting pain and disability after randomization in the prolonged conservative care group.

This study to investigate this scientific gap in our understanding of the effectiveness of surgery for LSRS is in line with a recommendation by the Dutch Health Council in 1999 to the Minister of Health [4] and the current Cochrane Review [15,16].

The results of this trial will lead to a more rational use of the existing guidelines if the hypothesis is rejected. If the latter is accepted and prolongation of the conservative treatment policy is more cost-effective than surgery after 6–12 weeks, the current guidelines for the timing of surgery need correction.

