## Methods/design

To answer the main research question the investigators propose to conduct a multi-centre comparative randomized clinical trial with parallel group design. The main research question will be answered after a follow-up of six months (Figure 1). The complete follow-up will last two years. The multi-centre design is necessary to collect enough patients in two years. The Medical Ethics Committee of all participating hospitals approved the study protocol.

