After the first consultation the GP will make a follow-up schedule. During the next visit the patient and doctor will look at the changes since the first visit to determine whether there is any improvement in the ability to perform normal activities. The doctor will check the efficacy of the prescribed pain medication and may adjust the dose or sort of analgesics according to the NHG guidelines. In these guidelines paracetamol is the first choice. If not effective, NSAID's (ibuprofen, diclofenac or naproxen) are to be prescribed. Only in the event of severe disabling pain morphine may be given for a restricted period of time. By preference all analgesics should be taken at fixed times of the day rather than on a 'if necessary' basis. If the GP and the patient conclude that there is considerable kinesiophobia because of the fear that the radicular or low back pain will increase, the help of a physiotherapist can be recommended. Guided by the GP (and physiotherapist) the patient will upgrade his or her activities according to the agreed time schedule [25,26]. The guide will be time, not the intensity of the pain. The GP will be free in her/his choice of prescription of medication and referral to physiotherapists. The research nurse will register the conservative management strategy after communication with the responsible GP. In case of progressive neurological deficit or worsening intolerable pain the GP can refer the patient back to the research nurse or neurosurgeon. If, six months after randomization, the patient has still not improved or suffers from intermittent LSRS, surgical treatment will be offered. Some patients will ask for surgery earlier because of worsening drug resistant leg pain. In these cases and in the case of a progressive neurological deficit, surgery will be performed in consultation with the patient. If after maximum conservative treatment and counselling the patient is still not able to cope with the functional disability surgery can be requested. If surgery in these cases is not offered by the study-group the patient does have the right to have a second opinion with an undependable neurosurgeon of another university hospital.

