### Outcome assessment

In the LSRS the most common complaints are pain and disability to perform normal daily activities. We will use below described validated outcome parameters, which will be assessed by means of questionnaires. Patients are not informed about their earlier scores. Follow-up examinations by the research nurse will take place 8, 26 and 52 weeks after randomization and the patients will keep a diary (table 2). In between at 2, 4, 12, 38, and 78 and after 104 weeks the main questionnaire (primary outcome measures) will be filled in at home and send to the data centre.

**Table 2 T2:** Data collection and outcome measures

Time in weeks	?	0	2,4	8	12	26	38	52	78	104
Likert	**X**	**X**	**X**	**X**	**X**	**X**	**X**	**X**	**X**	**X**
Neurological examination		**X**		**X**		**X**		**X**		
Severity of complaints (VAS)	**X**	**X**	**X**	**X**	**X**	**X**	**X**	**X**	**X**	**X**
McGill	**X**									
Health Status (SF 36)	**X**			**X**		**X**		**X**		**X**
Functional Status (RDQ)	**X**	**X**	**X**	**X**	**X**	**X**	**X**	**X**	**X**	**X**
EuroQol/VAS Q-of-life	**X**	**X**	**X**	**X**	**X**	**X**	**X**	**X**	**X**	**X**
MRI		**X**							**X**	
Costs	**X**	**X**	**X**	**X**	**X**	**X**	**X**	**X**	**X**	**X**
Prolo	**X**			**X**		**X**		**X**		
Complications		**X**		**X**		**X**		**X**		
Surgery				**X**		**X**		**X**	**X**	**X**
SFBI	**X**	**X**		**X**		**X**		**X**		**X**

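### Recording complications only when attributed to treatment may favour prolonged conservative care by an unknown amount, and operations after week 52 have no scheduled complication record

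*Protocol article*

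**What the plan says.** All references are to the protocol article.

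- **What is recorded.** Other outcome measures, item 3: "Side-effects or complications that are ascribed to the treatment are recorded by the patients, their treating physicians and the research nurses".
- **Who judges.** Treatment allocation says that patients, their doctors and the research nurses cannot be blinded. These are the same three groups that record complications.
- **When.** Outcome assessment: "Follow-up examinations by the research nurse will take place 8, 26 and 52 weeks after randomization". At the remaining time points, including weeks 78 and 104, "the main questionnaire (primary outcome measures) will be filled in at home and send to the data centre". In Table 2 the complications row is marked at weeks 0, 8, 26 and 52, and the surgery row at weeks 8, 26, 52, 78 and 104.
- **Length of follow-up.** Methods/design: "The complete follow-up will last two years".
- **Deterioration under waiting is foreseen.** Conservative management: "In case of progressive neurological deficit or worsening intolerable pain the GP can refer the patient back to the research nurse or neurosurgeon".
- **Why complications matter here.** The Background lists the effects on return to work, "as well as the complications of both strategies have not yet been investigated". The Discussion adds that the comparison is between healthcare strategies and not between treatments.

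**The concern.** There are two separate problems.

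**Attribution as a filter.** When strategies are compared, the harm of waiting includes what the disease does while the patient waits. Conservative care in this trial is information, advice to stay active, analgesics and sometimes physiotherapy. If a deficit worsens under that care, most observers would blame the herniation. If one appears after discectomy, most would at least consider the operation. A rule that admits an event only after such a judgement, made by people who know the allocation, can treat the same event differently in the two arms.

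**Different end dates.** Operations are followed for two years and complications for one. An operation in the second year adds to the surgical count, but nothing in the schedule asks whether it went badly.

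The Background presents the trial as a trade-off between faster relief of leg pain on one side, and lower cost and avoidance of surgery's negative effects on the other. The complication comparison feeds the second side of that trade-off.

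**Working it through.** The article gives no figure to reproduce on this point. The check sets the schedule rows side by side and follows the attribution rule through each arm.

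**Step 1. Schedule (Table 2, scheduled weeks from randomization).**

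| Item | Weeks marked | Last week |
|---|---|---|
| Complications | 0, 8, 26, 52 | 52 |
| Neurological examination | 0, 8, 26, 52 | 52 |
| Surgery | 8, 26, 52, 78, 104 | 104 |
| Sciatica Frequency and Bothersome Index | 0, 8, 26, 52, 104 | 104 |

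One mark elsewhere in the table may be misplaced: the follow-up MRI stands under week 78, while the text says 52 weeks. The complications row, however, agrees with the nurse visits given in the text (8, 26 and 52), so its end at week 52 can be relied on.

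**Step 2. Window by arm.** Counted from randomization, scheduled complication recording lasts 52 − 0 = 52 weeks in group A and 52 weeks in group B. The difference between arms is 0.

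**Step 3. Window by operation.** For an operation at week s, the scheduled complication window is max(0, 52 − s), and the period over which surgery is still counted is 104 − s.

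| Operation at week | Complication window | Surgery still counted for |
|---|---|---|
| 2 (latest planned in group A) | 50 | 102 |
| 26 (six-month offer in group B) | 26 | 78 |
| 52 | 0 | 52 |
| 78 | 0 | 26 |

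The uncovered stretch is 104 − 52 = 52 weeks, half of the two-year follow-up. It applies to delayed first surgery in group B and to re-operation in either arm.

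**Step 4. How many events.** The number falling outside the schedule is n × r × c, where n is patients per arm (150 planned, Sample size), r is the share operated after week 52 and c is the complication rate per operation. The article gives neither r nor c. Purely as an assumption for scale, r of 10% to 40% and c of 5% to 20% give 150 × 0.10 × 0.05 = 0.75 to 150 × 0.40 × 0.20 = 12 events in an arm. Nothing in the article supports these ranges, and the conclusion does not rest on them.

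**Step 5. The attribution rule in each arm.** Take a new or worse deficit. In group A it follows an operation and can readily be ascribed to it. In group B it follows advice and analgesics and is more naturally ascribed to the disease, in which case it does not meet the stated condition for recording. The likely direction is a lower recorded count in group B. The size depends on how often deficits progress and how recorders judge them, and the article gives neither.

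**The case against.** The strongest case against has five parts.

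1. **Harms of waiting are visible elsewhere.** The neurological examination at weeks 8, 26 and 52 records deficits in both arms whatever their cause. The Sciatica Frequency and Bothersome Index has weakness and numbness items and is repeated at week 104. The Roland score and leg pain also run to week 104, and the surgical rate in group B is itself read as success or failure of that policy. This stands, and it limits the damage. But these are not the complication count, and the examination also stops at week 52.

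2. **The schedule does not favour an arm.** A reader might infer from 50 weeks after surgery in group A against 26 weeks after a six-month operation in group B that the schedule itself is biased. The document does not support that reading. Analysis is by intention to treat, strategies are compared, and both arms have the same 52 weeks from randomization. Time since operation is the clock for comparing operations. Group B patients operated early for worsening also have more than 26 weeks. This objection stands in full.

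3. **The late gap is not peculiar to group B.** Re-operations in group A after week 52 are equally unscheduled, and the six-month offer falls inside the recorded year. This stands too.

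4. **The direction of the attribution effect is not proven.** Harm from delay could be ascribed to the allocated conservative treatment, side-effects of analgesics would qualify, and a persisting deficit in group A could be blamed on the disease. This makes the direction likely rather than certain.

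5. **A design article is brief.** Detailed event definitions may stand in the full protocol, and item 3 sets no end date for recording by patients and physicians. Late events could therefore be reported spontaneously. However, the article does state a condition for recording and a schedule, and both can be judged as written. Spontaneous reporting is not systematic ascertainment.

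**Conclusion.** The point holds in two limited parts.

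First, recording complications subject to unblinded attribution does not suit a comparison of strategies. It may make prolonged conservative care look safer than it is. The size cannot be estimated from the document, and the neurological examination and the symptom index offset it in part. This rests on one assumption: that progression during waiting is ascribed to treatment less often than a deficit after surgery.

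Second, complications of any operation between weeks 52 and 104 have no scheduled record, although the operation is counted. This follows directly from Table 2 and the visit schedule. It affects both arms, and the number of events is unknown.

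A reader might go further and infer that harms of waiting go unseen altogether. The cause-independent measures in the same table rule that out. The primary analysis is untouched. This is a cheap improvement to a safety comparison that the Background names as a gap in knowledge.

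**What to change.** - **Reword item 3** so that attribution no longer decides what is recorded. Count prespecified events in both arms from randomization, whatever the presumed cause: new or worsened neurological deficit, cauda equina syndrome, peri-operative events and other serious events. Keep attribution as a descriptor of each event.
- **Add a complications item** to the home questionnaires at weeks 78 and 104, where surgery is already recorded. Coverage after an operation then becomes 104 − s weeks: 102 for surgery at week 2, 78 at week 26, 52 at week 52 and 26 at week 78.

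The cost is one rewording and one item on two questionnaires that are already sent. The downside is that more events unrelated to either strategy will have to be listed. Only measurement changes; clinical management stays as it is.

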### Sample size

The result of this study is based on the short-term success of surgical intervention and will be a trade-off between a quicker relief of leg pain versus an advantage in cost-effectiveness for conservatively managed patients. The sample size is calculated on the basis of the Roland Disability Questionnaire for Sciatica averaged during the 12 months follow-up period. The numbers used for this sample-size are drawn from the Maine Lumbar Spine Study 1 year and recently published 5-year results [19,55]. The difference in the Roland score between the surgical- and non-surgical group in this study did not change between 3 and 12 months follow-up as shown in their study [19] and can be averaged over the first year. The main aim of this study is to measure the short-term functional difference at 12 months follow-up. Surgical treatment is considered better when the post treatment change is at least 4 points more when compared to the conservative treatment arm [38] and constant over time. Considering this constant difference and a mean standard deviation =10 over the first year [55] 140 patients per treatment arm are needed to reach a power (1-β) of 0,90 with α = 0.05 (two-sided). To answer the main research question 280 patients are needed for analysis with at least 12 months follow-up. The aim is to enrol 300 (150 per arm) patients in the study, including 8 % loss to follow-up after 1 year. The total number of operated patients each year in all participating hospitals exceeds 1400. With this number of patients also a clinically important difference in median time to recovery of two months can be detected by survival analysis. Although the time to recovery is the main issue, the problem of recurrent complaints is still not solved in the different approaches of survival and proportional hazard analysis.

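### Minor, but wrong as written: the printed inputs give 132–133 per arm, not 140, and 280 analysable, 300 enrolled and 8% loss do not agree; 90% power is not at risk

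*Protocol article*

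**What the plan says.** All the figures are in the protocol article, section Sample size.

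- **Outcome:** "The sample size is calculated on the basis of the Roland Disability Questionnaire for Sciatica averaged during the 12 months follow-up period".
- **Difference:** "Surgical treatment is considered better when the post treatment change is at least 4 points more when compared to the conservative treatment arm".
- **SD:** "mean standard deviation =10 over the first year", taken from a cited observational study.
- **Result:** "140 patients per treatment arm are needed to reach a power" of 0.90, at a two-sided alpha of 0.05.
- **Total for analysis:** "To answer the main research question 280 patients are needed for analysis", each with at least 12 months of follow-up.
- **Enrolment:** "The aim is to enrol 300 (150 per arm) patients in the study", which is said to cover 8% loss to follow-up at one year.

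The section names no test or formula. It mentions no rounding margin and no inflation other than the loss to follow-up.

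**The concern.** The article prints every input that a two-group comparison of means needs, so the result can be checked directly. Two steps do not come out. The number per arm is higher than the inputs require, and the loss allowance cannot explain it because that is added afterwards, between 280 and 300. That later step does not close either: at the plan's own loss rate, 300 enrolled leaves fewer than the 280 said to be needed.

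The stake is how the completed trial will be judged. The requirement is overstated for the printed inputs, and the allowance for loss is understated for the printed loss rate. A reader therefore cannot tell from the paragraph how much loss the trial can really absorb.

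**Working it through.** **Inputs** (all from Sample size): difference 4, SD 10, two-sided alpha 0.05, power 0.90, equal arms, 280 for analysis, 300 enrolled, loss 8%.

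**1. The plan's figure of 140 per arm**

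Normal formula: n per arm = 2 × (z for alpha + z for power)² × (SD / difference)²

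= 2 × (1.960 + 1.282)² × (10 / 4)² = 131.3, so 132.

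The t-test solution is 132.3, so 133. The total is 264–266, and 140 is not reproduced by either method. A one-sided test gives 108, which is further away. Against 132–133, the printed 140 is 7–8 per arm higher (7/133 = 5%, 8/132 = 6%).

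Read the other way, power for a difference of 4 and SD 10 is:

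| Per arm | Normal | t-test |
|---|---|---|
| 132 | 0.901 | 0.899 |
| 133 | 0.904 | 0.901 |
| 138 | 0.914 | 0.912 |
| 140 | 0.917 | 0.915 |

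**2. What would produce 140**

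- SD of about 10.3 with a difference of 4: 131.3 × 1.03² = 139.3, so 140.
- Difference of about 3.87 with SD 10.
- An allowance for a rank test (relative efficiency 0.955): 132 / 0.955 = 138.2 or 132.3 / 0.955 = 138.5, so 139. This is close but not 140, and the article names no rank test.

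If the printed SD of 10 is a rounded value (an assumption), the true value lies between 9.5 and 10.5. The requirement then runs from 131.3 × 0.95² = 118.5, so 119, to 131.3 × 1.05² = 144.8, so 145 per arm. The printed 140 lies inside that range.

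**3. The step from 280 to 300**

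- 300 × (1 − 0.08) = 276, or 138 per arm, which is 4 short of 280 (4/280 = 1.4%).
- Enrolment needed for 280 after 8% loss: 280 / 0.92 = 304.3, so 305. The cruder 280 × 1.08 gives 303.
- Loss that 300 can bear and still leave 280: 20 / 300 = 6.7%. As an addition to 280 it is 20 / 280 = 7.1%. Neither rounds to 8%.

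**4. Real margin on the printed inputs**

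With 266 sufficient for 90% power, 300 enrolled tolerates (300 − 266) / 300 = 11.3% loss. The smallest enrolment that covers 8% loss is 266 / 0.92 = 289.1, so 290.

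**The case against.** The strongest reply is that neither figure is an error of substance. The SD is described as a mean over the first year and is printed as a whole number. An unrounded value near 10.3 would give 140 exactly. The figure may also have been rounded up, or carry a margin recorded in the full protocol that this article condenses. It is conservative in any case: 140 per arm does deliver at least 90% power. In the loss step, 300 is a round recruitment target that misses 280 by four patients. The section Statistical and cost analysis also keeps withdrawn patients in the analysis until they withdraw, so they are not wholly lost.

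Much of this stands. It rules out calling 140 a proven mistake, and it rules out simply striking the 280, since that would assume 140 contains no allowance. It does not remove the point. The article presents 140 as what the printed inputs require, and on those inputs it is not. No rounding of the SD reconciles 280, 300 and 8%. Keeping partial data does not help here, because the section asks for 280 patients with at least 12 months of follow-up.

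A reader might also infer that the trial misses its target and is underpowered, or should enrol 305. The documents do not support that. The expected 276 falls short only of the printed 280; it exceeds the 264–266 that the printed inputs require.

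**Conclusion.** The point holds as a minor reporting error. On the printed inputs the requirement is 132–133 per arm, and the stated 140 gives about 91.5% power. The figures 280, 300 and 8% are mutually inconsistent by four patients. Under the stated assumptions 90% power is not at risk: 138 per arm gives 91.2% (t-test) to 91.4% (normal).

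This rests on a two-sample comparison of means with equal arms and on an SD of 10 as printed. If the SD behind 140 was in fact about 10.3, then 140 was right and 276 analysable would sit marginally under the target: the test statistic is expected at 4 / (10.3 × √(2/138)) = 3.226, and 3.226 − 1.960 = 1.266 corresponds to about 89.7% power. That is still a trivial shortfall, but it is a reason to state which SD was used.

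**What to change.** Reword the Sample size paragraph and leave enrolment at 300.

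1. For the requirement, choose one:
   - give 133 per arm (266 analysable) as the number for 90% power with a 4-point difference and SD 10; or
   - keep 140 per arm (280 analysable) and state the unrounded SD or the margin that produces it.
2. For the loss step, in either case, say that 300 enrolled with 8% loss leaves 276 analysable (138 per arm), with about 91% power at SD 10. Alternatively, if 280 is kept as the requirement, correct the loss allowance to 6.7%.
3. Name the test or formula used, so that the figure can be reproduced.

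The cost is the wording of one paragraph. No patient numbers, procedures or analyses change.
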